## Abstract

**Background:**  Dengue is a disease of major global importance. While most symptomatic infections are mild, a small proportion of patients progress to severe disease with risk of hypovolaemic shock, organ dysfunction and death.  In the absence of effective antiviral or disease modifying drugs, clinical management is solely reliant on supportive measures. Obesity is a growing problem among young people in Vietnam and is increasingly recognised as an important risk factor for severe dengue, likely due to alterations in host immune and inflammatory pathways. Metformin, a widely used anti-hyperglycaemic agent with excellent safety profile, has demonstrated potential as a dengue therapeutic
*in vitro* and in a retrospective observational study of adult dengue patients with type 2 diabetes.  This study aims to assess the safety and tolerability of metformin treatment in overweight and obese dengue patients, and investigate its effects on several clinical, immunological and virological markers of disease severity.

**Methods:** This open label trial of 120 obese/overweight dengue patients will be performed in two phases, with a metformin dose escalation if no safety concerns arise in phase one. The primary endpoint is identification of clinical and laboratory adverse events.  Sixty overweight and obese dengue patients aged 10-30 years will be enrolled at the Hospital for Tropical Diseases in Ho Chi Minh City, Vietnam. Participants will complete a 5-day course of metformin therapy and be compared to a non-treated group of 60 age-matched overweight and obese dengue patients.

**Discussion:**  Previously observed antiviral and immunomodulatory effects of metformin make it a promising dengue therapeutic candidate in appropriately selected patients. This study will assess the safety and tolerability of adjunctive metformin in the management of overweight and obese young dengue patients, as well as its effects on markers of viral replication, endothelial dysfunction and host immune responses.

**Trial registration:** ClinicalTrials.gov:
 NCT04377451 (May 6
^th^ 2020).

## Background

Dengue is a major threat to global public health, with an estimated annual incidence of 390 million infections worldwide, leading to approximately 96 million symptomatic cases and 22,000 deaths in more than 120 countries
^1^. Despite increasing understanding of dengue pathogenesis, effective anti-viral or disease modifying agents are yet to be identified, and patient management remains reliant on judicious fluid replacement in response to plasma leakage during the critical phase of illness (usually days 4–6)
^2,
3^.

While the vast majority of symptomatic infections give rise to the milder form of disease, dengue fever, those that progress to severe disease carry significant risk of vital organ dysfunction and death. Several patient groups have been identified as being at particular risk of severe dengue, including the elderly, pregnant women, those with comorbid illness, and those with prior exposure to alternative dengue serotypes
^4^. An important and increasingly recognised severe dengue risk factor is obesity, a condition which has had a dramatic increase in prevalence among Vietnamese children and adolescents over the last two decades
^5^. Several observational studies have reported an association between obesity and severe dengue
^6–
9^. A recent systematic review and meta-analysis reported the odds of developing severe dengue to be significantly higher in obese children in comparison to their non-obese counterparts (OR = 1.38; 95%CI 1.10 - 1.73)
^10^.

The underlying mechanism remains unknown, but could possibly be explained by chronic low-grade inflammation that is induced by being overweight or obese
^11,
12^. Adipocytes are known to produce pro-inflammatory cytokines and adipokines, such as adiponectin, resistin and leptin, each of which have a role in immunomodulation. Obesity-induced leptin and resistin are known to be associated with many of the physiological abnormalities seen in dengue, including platelet dysfunction, vascular inflammation, myocardial injury, endothelial dysfunction
^13–
16^, and capillary hyper-permeability
^17–
19^. Additionally, it is possible that more severe infection is permitted by altered CD8
^+^ T cell immunity and impairment of natural killer (NK) cell activity in obese hosts
^20,
21^.

Adenosine Monophosphate (AMP)-Activated protein kinase (AMPK) is an enzyme involved in maintaining cellular energy homeostasis, in particular lipid metabolism, protein synthesis and glucose metabolism, and has been linked to anti-inflammatory processes
^22^. Obesity has been shown to down-regulate AMPK, either as a result of fatty acid, amino acid and glucose accumulation
^22^, or due to an increase in circulating pro-inflammatory cytokines
^22,
23^. One consequence of AMPK down-regulation is the inhibition of lipid catabolism and subsequent boosting of
*de novo* lipid synthesis, creating conditions that favour viral replication and survival within host cells
^24,
25^.

With the majority of symptomatic dengue infections leading to mild, self-limiting illness, development of novel treatment strategies should focus on patient groups at the highest risk of severe disease
^26^. This study aims to assess the effect of metformin, a drug known to attenuate inflammatory processes particularly in the context of obesity, on the disease course of dengue in overweight and obese children and young adults.

### Metformin

Metformin (dimethybiguanide) is an oral anti-hyperglycaemic agent. Its mechanism of action is complex and only partially understood, but AMPK activation is recognised as one of a number of key processes in modulating glucose metabolism
^27^. After sixty years of use as the first-line drug to manage type 2 diabetes mellitus (T2DM), metformin has proven to have an excellent safety and tolerability profile, while also demonstrating potential to have further therapeutic applications through its broad range of pleiotropic effects. These include antioxidant, anti-inflammatory and immunomodulatory properties, as well as aiding endothelial vascular reactivity and preservation of the glycocalyx layer
^28–
30^.

Evidence regarding the effectiveness of metformin in treating obesity is well established. The drug has demonstrated utility in inducing both significant weight loss and a reduction in the inflammatory biomarkers interferon-γ, total plasminogen activator inhibitor-1 (PAI-1) and the adiponectin–leptin ratio in obese adults with or without T2DM
^31–
33^.

Other studies have shown improved clinical outcomes with metformin use in a number of infectious diseases, including hepatitis C (HCV), tuberculosis and dengue
^34–
39^. Notably, the use of metformin as an adjunct in the treatment of patients with HCV and insulin resistance has been shown to improve rates of sustained virological response in comparison to standard anti-viral treatment alone
^40^. Furthermore, two prospective trials of metformin use in patients with HCV and T2DM have demonstrated significant reductions in liver-related complications
^35,
36^.

### Metformin and dengue

Several of the aforementioned effects of metformin treatment have prompted consideration of its use as a potential dengue therapeutic. Firstly, the replication of dengue virus has been shown to be restricted by inhibition of lipid synthesis through AMPK activation
^24,
41^. Furthermore, metformin’s immunomodulatory effect, which facilitates NK cell activation, reduces T cell exhaustion profiles and enhances CD8
^+^ T cell memory, could help reduce levels of peak dengue viremia and shorten viral clearance times
^39,
41,
42^.

Metformin is rapidly absorbed and eliminated as an oral formulation and steady state is usually achieved within 24 hours. Metformin has been shown to decrease dengue viral genome copies in a dose-dependent manner
*in vitro* via activation of AMPK, with 90% reduction in NS1 secretion in infected cells after 24 hours of treatment
^41^. In obese/overweight adolescents, time to peak concentration and absorption, appears to be faster than non-obese children
^43^. In addition, anti-viral effects using a 5 day course of metformin has also been demonstrated in a mouse model of coxsackievirus B3 (CVB3) infection, through rapid action on AMPK activation
^44^.

Prevention of progression to severe dengue by attenuating the inflammatory mediators leptin and resistin is also plausible
^45^. Additionally, metformin could help reverse endothelial dysfunction, a hallmark feature of dengue pathogenesis, by improving endothelial-dependent vasodilation and reducing expression of endothelial vascular cell adhesion molecule (VCAM) and intercellular adhesion molecule 1 (ICAM1)
^24^. Recent observational evidence suggests metformin use in adult dengue patients with T2DM is associated with reduced risk of developing severe dengue (adjusted RR = 0.60, 95%CI 0.37-0.98)
^37^. However, the mechanisms underlying this association, and any relationship they have to obesity, require further investigation.

### Aims of the trial

We hypothesize that metformin therapy given early in the course of disease will attenuate obesity-induced lipid-inflammatory mediators and improve clinical parameters in dengue patients with obesity. In addition, the therapy could reduce viral replication through AMPK activation and immunomodulation in such patients.

This study aims to formally assess metformin as adjunctive therapy for dengue in overweight and obese patients.

## Methods/design

This is protocol version 4.0, dated February 10
^th^ 2020.

### Design

This is an open-label study investigating metformin therapy in 60 overweight and obese Vietnamese adults (30 patients) and children (30 patients). Age range of 10 to 30 years, who are admitted to the Hospital for Tropical Diseases (HTD) in Ho Chi Minh City (HCMC), Vietnam, with positive non-structural protein 1 (NS1) rapid test and onset of fever <72 hours prior to admission.

We will investigate the effects of five days of metformin treatment on the grounds that the critical phase of disease usually occurs around the fifth day of illness.

The trial will be conducted in two phases, with a dose escalation between phases (
Figure 1). In the initial phase (cohort 1), five young adults (age ≥16) and five children (age <16) with body mass index (BMI) >25 kg/m
^2^ (BMI-for-age >1 standard deviation – SD) will be provided with a low dose of metformin once daily at 850mg and 500mg, respectively. If the five-day safety and clinical data of cohort 1 show no safety concerns, the study will progress to the second phase (cohort 2). This will include 25 adults and 25 children, who will be given a weight-based dose of metformin; 1000mg (500mg twice daily) for participants with weight <60kg, and 1500mg (1000mg mane, 500mg nocte) for those ≥ 60kg. Of note, the actual number of patients in each cohort will depend on the results of safety reviews. Recruitment is expected to happen over two dengue seasons, and discharged patients will be asked to return for a single outpatient follow-up (FU) visit around day 28 of illness.

**Figure 1. f1:**
[figure not shown]
Trial flow chart.

The 60 patients receiving treatment will be compared to 60 overweight or obese patients with standard of care (without treatment) recruited contemporaneously from the same wards, with the same enrolment criteria, in an ongoing observational study as the control arm.

### Inclusion and exclusion criteria

Patients will be eligible for study enrolment if they: (i) are aged between 10 and 30 years; (ii) have a clinical diagnosis of dengue (based on World Health Organization (WHO) – Dengue guidelines)
^2^; (iii) are NS1 rapid antigen test positive; (iv) have BMI >25kg/m
^2^ (or BMI-for-age >1 SD); (v) are admitted within 72 hours of fever onset; (vi) agree to come back for FU visit between days 21–28 of illness; and (vii) provide written informed consent.

Exclusion criteria include: (i) pregnancy (confirmed by either clinical examination or urine dipstick for human chorionic gonadotrophin hormone); (ii) localising features suggestive of an alternative diagnosis; (iii) significant diarrhoea and/or vomiting (>3 episodes/24 hours); (iv) history of hypersensitivity to metformin; (v) current use of metformin or any other regular hypoglycaemic agent, including insulin; (vi) current use of any drug with significant metformin interaction (
*Extended data*
^46^); (vii) current treatment for heart failure or recent history of myocardial infarction (in the last year); (viii) presence of severe infection at enrolment, including severe dengue, central nervous system infection or septicaemia; (ix) baseline lactate level >2.0 mmol/L; (x) baseline blood glucose level <3.9 mmol/l (or <70 mg/dL); (xi) baseline liver impairment (alanine transaminase (ALT) and/or aspartate transaminase (AST) >250 U/L); and (xii) chronic renal impairment (glomerular filtration rate (GFR) <30 mL/min). Patients that are deemed unlikely to attend FU at 28 days from fever onset because of long travelling distance to the clinic will also be excluded.

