### Screening, enrolment and retention

Patients aged between 10 and 30 years that are admitted to one of the three study wards of the HTD, HCMC, Vietnam, with clinical suspicion of dengue and less than 72 hours of fever are invited to participate in the trial. After giving consent, patients are screened for their eligibility to commence treatment with the trial drug by the study physicians. Blood samples are collected to test for NS1, and AST, ALT and creatinine levels and in female patients, a urine sample is collected for a pregnancy test. Glucose and lactate levels are measured using point-of-care (POC) tests.

All patients will be asked to come back for a final FU visit at 28 days after the onset of fever. Patients will be contacted 3–5 days prior to the FU visit to arrange an appropriate appointment date and time. Any case who misses the FU visit will be contacted by phone either to reschedule the visit or to collect information if patients could not arrange their time to come back. If the patients stay in the hospital for longer than 5 days, due to AEs or any other reason, the treatment for these cases will be at discretion of the attending physicians. No further blood samples or study procedures will be performed from this point onward. However, the final outcome at discharge will be collected in the case report form (CRF;
*Extended data*
^46^).

At discharge, the participants will be offered a referral to nutrition specialists for a consultation of overweight/obesity management. Patients will also be provided with leaflets on healthy eating and lifestyle behaviours.

While not an RCT, this trial is designed to enroll patients contemporaneously with an observational obesity trial, where patients received standard care, to minimize systematic differences between the intervention (metformin) and control group, i.e. patients have the same inclusion /exclusion criteria, enrolled on same wards, with the same standard of care during the same dengue season (to avoid the issue of viral serotype shifts). 

To minimize selection bias, we have set up a system on the dengue wards, to ensure eligible patients are recruited into both studies in a systematic way. This involves only one study enrolling for a 2-week time block. During that time, if a patient fails screening assessment or declines enrollment into one of the trials, they are not eligible for the other.

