In addition, we will ensure the predefined inclusion/exclusion criteria for all patients enrolled are strictly adhered to reduce investigator subjective assessment and will carefully document screen failures and all exclusions and withdrawals in the trial. And lastly, we plan to have an intention-to-treat analysis where independent study investigators will perform a blinded outcome assessment for all patients.

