### Safety reviews

The trial will be conducted in two phases, with a dose escalation if no safety concerns arise during the low dose stage. Metformin dosing will begin at 500mg (children) and 850mg (adults) once daily for 5 days in cohort 1. Daily patient safety reviews will be performed by study doctors using clinical and laboratory data to decide whether patients are safe to continue taking the study drug.

The study drug will be stopped if participants: (1) request withdrawal from the study; (2) develop any AEs, including severe renal impairment (GFR below 30mL/min/1.73m
^2^), elevated lactate to ≥ 3 mmol/L, severe liver involvement (AST/ALT > 400U/L), severe diarrhoea (≥ 5 episodes of loose stool/day), persistent vomiting (≥ 3 episodes/hour or ≥ 4 / 6hours) and hypoglycaemia (blood glucose < 3.9 mmol/l or < 70 mg/dL); (3) develop severe dengue (defined as admission to intensive care unit); or (4) are intolerant of metformin.

All AEs occurring during the trial/or until the FU visit at around day 28 of illness, will be recorded in the CRF, and whether or not attributed to trial medication. Specific AEs are shown in
Table 1. Laboratory events will be graded according to Common Terminology Criteria for Adverse Events (CTCAE) definitions. Clinical events will be assessed as mild, moderate, or severe. If the event is serious and not only related to the progression to severe dengue, or is fatal, then a serious AE form must be completed and the OUCRU CTU notified within 24 hours.

In cases of discontinuation due to AEs, participants will be followed up until the events have resolved or stabilised. A Data Monitoring Committee (DMC) review will take place after day 5 data is fully available for the first ten patients enrolled in cohort 1. Following satisfactory safety review of the tenth patient, metformin doses for all remaining patients (cohort 2) will be weight-based; 5 days of 1000mg (500mg twice daily) for those weighing <60kg and 5 days of 1500mg (1000mg mane, 500mg nocte) for those weighing ≥60kg. All AEs and serious adverse events (SAEs) will be recorded and reported to the Ethics Committees (ECs) for review. Further DMC meetings will take place 6 monthly to review enrolment, AEs, treatment received and FU information, and any other requested data.

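### Renal exclusion (xii) is worded for chronic impairment only, so read literally it does not exclude an acute GFR below 30 at screening, the level at which metformin is stopped (low-severity wording error)

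*Protocol article*

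**What the plan says.** All references are to the protocol article.

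- **Inclusion and exclusion criteria.** The only renal exclusion, (xii), is "chronic renal impairment (glomerular filtration rate (GFR) <30 mL/min". The three laboratory exclusions just before it are tied to the baseline value: "baseline lactate level >2.0 mmol/L; (x) baseline blood glucose level <3.9 mmol/l (or <70 mg/dL); (xi) baseline liver impairment", the last defined as ALT and/or AST above 250 U/L. Exclusion (viii) is "presence of severe infection at enrolment, including severe dengue, central nervous system infection or septicaemia", with no renal limit. Exclusion (iii) removes patients with significant diarrhoea or vomiting.
- **Screening, enrolment and retention.** After consent, "patients are screened for their eligibility to commence treatment with the trial drug by the study physicians". The tests follow: "Blood samples are collected to test for NS1, and AST, ALT and creatinine levels", with point-of-care glucose and lactate. The section also undertakes that "the predefined inclusion/exclusion criteria for all patients enrolled are strictly adhered to reduce investigator subjective assessment".
- **Safety reviews.** The drug is stopped if participants "develop any AEs, including severe renal impairment (GFR below 30mL/min/1.73m" (the squared sign follows in the text). Nothing is said about chronicity.
- **Primary endpoint, Table 1, item 11.** Acute kidney injury is a listed adverse event. One of its limbs is an eGFR below 30 mL/min/1.73 m², with no fall from baseline required.
- **Treatment and drug dispensation.** The first dose is to follow enrolment without delay.
- **Data collection.** Full blood count, glucose and lactate are daily. Creatinine is on alternate days, with extra tests when clinically indicated.

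**The concern.** An entry criterion for a drug should not admit a patient who already meets the rule for stopping it. The protocol treats a GFR below 30 as a reason to stop metformin, whatever its cause, yet the matching entry criterion applies only if the impairment is chronic.

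The qualifier carries meaning here because Table 1 names acute kidney injury as a category of its own. Patients enter within 72 hours of fever onset in an acute infection, so a raised creatinine at screening could well be acute.

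What is at stake is the safety of the first dose. The entry criteria are the check that comes before it, while the stopping rule concerns events that participants develop once on study. No estimate, power figure or analysis depends on the point.

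**Working it through.** The article gives no figure to reproduce, so the check sets the texts side by side.

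**1. Entry limits against stopping limits** (Inclusion and exclusion criteria; Safety reviews)

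| Measure | Excluded at entry if | Qualifier at entry | Drug stopped if |
|---|---|---|---|
| Lactate | >2.0 mmol/L | baseline | ≥3 mmol/L |
| Glucose | <3.9 mmol/L | baseline | <3.9 mmol/L |
| AST/ALT | >250 U/L | baseline | >400 U/L |
| GFR | <30 mL/min | chronic | <30 mL/min/1.73 m² |

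For the first three, every patient past the stopping limit at screening is excluded by the baseline limit. For GFR this holds only if the impairment is chronic. The size of the gap between entry and stopping limits says nothing about impact; only the qualifier matters here.

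**2. The literal path of one patient.** The screening creatinine gives a GFR below 30 and the impairment is acute. Exclusion (xii) does not apply as worded. Exclusions (iii) and (viii) apply only if the patient also has marked vomiting or diarrhoea, or a severe infection. The only definition of severe dengue in the article, given in the stopping rule, is intensive care admission. If neither applies, the patient is eligible and takes a first dose while already below the renal stopping level.

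**3. What acts after the first dose.** "Daily patient safety reviews will be performed by study doctors using clinical and laboratory data", and tests may be repeated when clinically indicated. The next scheduled creatinine, however, need not fall on the next day. These safeguards limit continued dosing but come after the first dose.

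**4. What the screening procedure implies.** Creatinine is measured in the eligibility work-up, and (xii) is the only criterion it can serve. A single value cannot show whether impairment is acute or chronic, and the article describes no earlier or repeat value before dosing. The practical reading is therefore that the bracketed limit of 30 applies to the screening result.

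**5. Unit (secondary).** Exclusion (xii) is in mL/min; the stopping rule and Table 1 are per 1.73 m². With body surface area BSA, the indexed value is GFR × 1.73 / BSA. The article gives no surface areas, so the following are assumed:

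- BSA 2.0 m²: 30 × 1.73 / 2.0 = 26 mL/min/1.73 m²
- BSA 1.73 m²: 30 × 1.73 / 1.73 = 30 mL/min/1.73 m²
- BSA 1.4 m²: 30 × 1.73 / 1.4 = 37 mL/min/1.73 m²

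In a large participant, an indexed GFR between 26 and 30 would pass (xii) even if chronic, yet meet the stopping limit. In a small child the entry limit would be the stricter of the two. The same rewording removes this mismatch.

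**The case against.** The strongest reply is that the screening procedure already answers the point. Each laboratory test listed there matches a criterion, and creatinine matches only (xii). If (xii) did not apply to the screening value, that test would serve no eligibility purpose. Staff cannot judge chronicity from one sample, so they would apply the only number stated. Exclusions (iii) and (viii) remove some of the likeliest acute cases, and daily review limits what follows. The article also condenses a full protocol, and the case report form in its extended data, not shown here, may already state the limit on the baseline value.

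Most of this stands, and it sets the severity. It does not make the wording right. The criterion is stated, not left to another document, and its qualifier differs from those of its neighbours and from the stopping rule. The commitment to adhere strictly to the criteria, made to limit subjective judgement at enrolment, sits poorly with a limit that works only if its qualifier is set aside.

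A reader might go further and infer that patients with an acute GFR below 30 will be dosed. The article does not support this: the screening creatinine makes the sensible reading the likely one in practice. Nor does it support an inference that the adverse event comparison is biased, since the control patients are recruited under the same enrolment criteria.

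**Conclusion.** The point holds as a low-severity error in the wording of a safety criterion. Exclusion (xii) carries a qualifier that the stopping rule and Table 1 do not, and a different unit. Taken literally, it leaves an acute GFR below 30 at screening without an entry limit.

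The number of patients affected cannot be derived from the article. That it should be very small is a judgement, resting on the age range of 10 to 30 years, on exclusions (iii) and (viii), and on the assumption that study physicians apply the limit of 30 to the screening value. The finding that the comparison is not biased rests on the statement that controls meet the same criteria. If the full protocol or case report form already applies the limit to the baseline value, the error lies in the article alone.

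**What to change.** Reword (xii) as: *baseline eGFR from the screening creatinine <30 mL/min/1.73 m², acute or chronic*. This brings it into line with (ix) to (xi) and with the unit of the stopping rule and Table 1. Use the same wording in the observational study that supplies the controls, so that the two groups keep identical criteria.

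The cost is one line of text and at most a few more exclusions. No new test is needed, because the screening creatinine is already taken. If the full protocol or case report form is already clear, only the article needs correcting.
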